### Child development assessment

The Ages and Stages Questionnaire Inventory (ASQ:I) will be administered at child ages 12 and 24 months to evaluate problem solving, communication, fine motor, gross motor, and personal social development in index children. The ASQ:I is a continuous sliding scale with questions for each domain and starts with the child’s chronological age followed by establishing a basal and ceiling levels of a child’s performance. Although it is a tool based on parents’ report, in Bangladesh, the ASQ:I was adapted by researchers to include a subset of items that are administered through direct assessment with locally available materials that the parents may not observe. Administration of the ASQ:I requires adequate training and around 45 minutes to administer. The adapted version of this instrument has been validated in Bangladesh (Pitchik et al. 2023). The Family Care Indicator (FCI) instrument will be used to measure the amount of stimulation the child receives at home at 12 and 24 months. This instrument measures stimulating activities, the availability of a variety of play materials, caregiver responsiveness and evaluates the child’s surrounding environment. This instrument has been validated in Bangladesh (Hamadani et al. 2010).

### Quality assurance for psychosocial measures

Child development and maternal bandwidth data will be collected by trained physicians and psychologists from icddr,b. All measurements will begin after pretesting in the community on non-study mother-child dyads (N=40), once an inter-observer agreement value of 90% is achieved between testers and trainers. Refresher training will take place every 6 months or when correlation coefficients for tester-supervisor pairs fall below 0.85. In a random sample of 5–10% of tests, testers’ evaluations will be compared to evaluations completed by trained psychologists.

### Video recording and analysis

We will record 6-hour video observations in a random subsample of 60 children (30 children per arm). Recording start times will vary from 7 AM to 12 PM between households to capture a wider range of activities and will be conducted in the household, courtyard, or near the courtyard. Observations will be paused during breastfeeding, bathing, and sleeping times. Videos will be coded to measure the duration, time, and location of relevant child activities, such as the soil contact and ingestion and animal contact, using LiveTrak software (Julian et al. 2018).

### Data management

Data will be collected on tablets using customized CommCare software, which facilitates longitudinal data collection. Data will be securely stored on CommCare servers and at icddr,b, with access limited to the study PI and the Data Manager. Paper records will be digitized and destroyed, and personal identifiers will be removed. Digitized materials will be stored indefinitely, with identifiable information password-protected and encrypted. Hard copies will be stored in locked cabinets. To ensure data quality, supervisors will observe interviews, conduct re-interviews, cross-check data, and provide feedback to enumerators. Field staff will maintain a field tracking form to track daily data collection activities. Stata and R scripts will regularly be used by the data manager, investigators, and statisticians to identify inconsistencies and errors, and errors will be resolved prior to analysis.

### Statistical analysis

To assess randomisation, we will compare the means and percentages of baseline characteristics between arms including maternal age, maternal education level, paternal education, paternal employment, housing wall and roof materials, household assets, acres of homestead land owned, household WASH infrastructure and access, open defecation practices, and deworming in the prior 6 months, animal ownership, and animal cohabitation.

The primary analysis will compare prevalence of any STH between study arms using an indicator for whether a child tested positive at the 6, 12, 18, or 24 month follow-up rounds. We will estimate the unadjusted prevalence ratio comparing intervention to control using generalized estimating equations (Zeger, Liang, and Albert 1988) with a binomial family and log link and an exchangeable correlation matrix to account for repeated measures within the same child. If log-binomial models do not converge, we will use modified Poisson regression with robust standard errors (Zou 2004). Secondary analyses will include indicators for follow-up rounds in order to estimate the prevalence ratio at each follow-up to assess whether effects vary over different child ages. All models will condition on geographic block and estimate robust sandwich standard errors (Freedman 2006) to account for the matched design (McNutt et al. 2003; Kernan et al. 1999). To assess whether the intervention effect is sustained over 2 years, we will also fit a model with an interaction term between treatment and follow-up time.

We will also compare secondary outcomes (Table 1) between study arms. For repeated measures outcomes, we will use generalized estimating equations (Zeger, Liang, and Albert 1988) with an exchangeable correlation matrix; we will estimate mean differences for continuous outcomes using an identity link and Gaussian family and prevalence ratios for binary outcomes using a log link and binomial family (McNutt et al. 2003). For measurements analyzed at a single time point, we will fit generalized linear models (McNutt et al. 2003) with a Gaussian family and identity link for continuous outcomes and a binomial family and log link for binary outcomes. If log-binomial models do not converge, we will fit models with a Poisson and log link (McNutt et al. 2003; Zou 2004).

Primary analyses will be unadjusted for covariates. A secondary analysis will adjust for baseline covariates to reduce bias associated with any chance imbalances between study arms at baseline and possibly increase efficiency (Pocock et al. 2002). We will pre-specify a potential covariate adjustment set of baseline variables and only adjust for covariates among this set that are associated with each outcome (likelihood ratio test p-value < 0.2).

Analyses will be intention-to-treat. The following households will be considered non-compliant: 1) control households that install concrete floors that cover at least one entire room inside the mother’s household; 2) households that cover at least one room’s floor with a cement finish; 3) intervention households that remove any part of the concrete floor installed as part of the trial; 4) intervention households in which a substantial portion of the concrete floor is damaged. If non-compliance exceeds 10% in either arm, we will perform a per-protocol analysis as well. We will not adjust for multiple comparisons because the number of outcomes is relatively modest, and the analysis will follow a pre-specified analysis plan.

We will compare attrition rates at each follow-up and across follow-ups between randomised arms and compare baseline characteristics of those lost to follow-up to those who complete the study. If there is evidence of systematic differences in attrition between arms and attrition exceeds 20%, we will explore whether study drop out resulted in selection bias using inverse probability of censoring weights with flexible machine-learning based estimation (Mark J. van der Laan 2011).

For STH measured in floor dust samples, the primary analysis will impute STH prevalence as 0 for floors that do not contain enough dust for nucleic acid extraction (0.1 g). The imputation assumes that floors with no dust do not harbor STH eggs. Our pilot data indicate that concrete floors in 40% of households may yield insufficient dust for nucleic acid extraction. We will conduct a secondary analysis by comparing STH outcomes in floor dust between intervention and control groups only using data from households where sufficient dust was obtained. We expect this analysis to yield a conservative estimate of intervention effectiveness because it will exclude intervention households with dust-free floors which are less likely to harbor STH eggs.

We will explore potential effect modification by the following baseline variables: household wealth, household WASH infrastructure, presence of animals inside the household, primary play location of children <2 years, index child sex, household distance to nearest permanent water body (Pekel et al. 2016), and ordinary portland cement vs. green cement. We will also assess effect modification by monsoon vs. dry season using a data-based definition and precipitation, temperature, and humidity levels (Nguyen et al. 2024) using weather station data from the Government of Bangladesh Meteorological Department. We will test for effect modification on the relative scale by including interaction terms between these variables and treatment group indicator variables in regression models. We will estimate additive scale interactions from log-linear models using the relative excess risk due to interaction (RERI) (Knol et al. 2011). To test for effect modification, we will estimate p-values on the interaction terms for relative scale interaction in log-linear models and for additive scale interaction RERIs (Knol et al. 2011; Assmann et al. 1996).

To assess whether any post-treatment variables mediate intervention effects, we will perform causal mediation analyses (Tingley et al. 2014) for the following potential mediators: deworming or antimicrobial consumption of birth cohort or other household members in the past 6 months, and floor coverings. Interim reductions in STH could result in reduced deworming use, which in turn, further reduces STH at the final follow-up measurement. Additionally, installation of concrete may alter the type and frequency of floor coverings used, which may influence health outcomes. We will also use causal mediation analysis to assess whether health and child development outcomes are mediated through environmental vs. maternal pathways. For the environmental pathway, mediators will include contamination of the home with *E. coli* and STH. For the maternal pathway, mediators will include maternal discretionary time use; maternal bandwidth (measures of executive function, inhibition, and working memory); and maternal quality of life, stress, and depression.

For the ASQi outcome, if child age varies substantially at each follow-up round, we will use age-specific Z-scores for each test within 2-month age bands and will control for age in the analysis. We will create reference distributions for each ASQi domain (communication, fine motor, gross motor, problem solving, and personal social) and the overall global scale. The sum of age-specific raw scores from the control group will be standardized with a mean of 0 and a SD of 1 for each 2-month age band. For the intervention arm, we will calculate standardized Z-scores using the reference distribution from the control arm in each age band. We will summarize the distribution of continuous outcomes (e.g., ASQi Z-scores) using Gaussian kernel density smoothers. We will estimate mean differences in ASQi scores or Z-scores between study arms using generalized linear models that condition on geographic block. To compare rates of attainment for each growth milestone, we will estimate hazard ratios using a semiparametric generalized additive model with a complementary log-log link and baseline hazard fit with a monotonic cubic spline.

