### Sample size calculation

The overall trial sample size was determined based on the primary outcome of prevalence of any STH at any follow-up (ages 6, 12, 18, 24 months). We estimated the required sample size using the standard formula for comparisons of two groups with repeated measures of a binary outcome (Liu and Liang 1997). From 2017-2020 in Sirajganj District, prevalence of *Ascaris lumbricoides* was 25.1%, and prevalence of *Trichuris trichiura* was <10% (Gerber et al. 2023). To be conservative, we assumed the prevalence of any STH in the control group over four follow-up rounds would be 20%. In our prior analyses of the association between concrete floors and any STH, the unadjusted prevalence ratio was 0.40 (95% CI 0.28, 0.56) (Benjamin-Chung et al. 2021), and the adjusted prevalence ratio was 0.73 (95% CI 0.52, 1.01) (Benjamin-Chung et al. 2015). We assumed a minimum detectable prevalence ratio of 0.70. We assumed intraclass correlation = 0.066 for repeated measurements of STH prevalence among children < 2 years (Platts-Mills et al. 2015). Assuming a Type I error = 0.05 and Type II error = 0.20, for a two-sided hypothesis test, the required number of households per arm is 336. Inflating this to account for 15% loss to follow-up and 10 households per randomisation block, the total required sample size across both arms is 800. 15% loss to follow-up was assumed based on the findings from the prior trial carried out by our team in rural Bangladesh (Luby et al. 2018), in which 6.5% of pregnant women miscarried or had still births, 3.5% of children died by 12-month follow-up, and <1% died between 12-24 months follow-up.

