### Participant retention

To minimize attrition in the control arm, we will compensate mothers from control households with 500 Bangladeshi Taka ($4.27 USD) after completion of each follow-up survey at 3, 6, 12, 18 and 24 months.

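### The primary repeated-measures model has no follow-up-round term, so missed stools that differ by arm and by age could modestly bias the pooled prevalence ratio in either direction

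*Protocol article*

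**What the plan says.** The Statistical analysis section describes the primary analysis as a GEE with log link, binomial family and "an exchangeable correlation matrix to account for repeated measures within the same child". All models condition on geographic block and use robust standard errors. The section adds: "Primary analyses will be unadjusted for covariates". Round is mentioned for other models: "Secondary analyses will include indicators for follow-up rounds in order to estimate the prevalence ratio at each follow-up". A separate treatment-by-time interaction model is planned to see whether the effect lasts.

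The Sample size calculation uses one value for all ages: "we assumed the prevalence of any STH in the control group over four follow-up rounds would be 20" per cent. It allows 15% loss to follow-up, supported by three figures from an earlier trial: 6.5% miscarriage or stillbirth, 3.5% child deaths by 12 months, and under 1% from 12 to 24 months.

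Participant retention describes a payment to control mothers after each follow-up survey, "To minimize attrition in the control arm". Attrition is to be compared between arms at each follow-up. Inverse probability of censoring weights are to be explored only if attrition differs systematically by arm and exceeds 20%.

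**The concern.** Without round terms, each arm's pooled prevalence is a weighted mean of its round-specific prevalences, and the weights are that arm's own completed stools. If infection becomes more common with age and one arm misses more of the late stools, that arm looks less infected than it is. More late losses in control would hide part of a real benefit; more late losses in the intervention arm would exaggerate a benefit or create one. This happens even when missingness depends only on arm and round, the simplest mechanism and one that round main effects handle. At stake is the trial's single primary estimate and its type I error.

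**Working it through.** **Inputs from the document.** Four stool rounds; true prevalence ratio (PR) 0.70 ("We assumed a minimum detectable prevalence ratio of 0.70"); two-sided alpha 0.05; within-child correlation 0.066; 15% loss; 800 households. The document has no figure for bias from age mix, so there is none to reproduce. On loss, 336/0.85 = 395.3, rounded up to 400 per arm, agrees with 800. One side remark explains the high power figures below. The usual repeated-measures formula with four rounds gives about 611 × (1 + 3 × 0.066)/4 = 183 per arm, or 183 to 194 across variants. Two rounds give 326 to 345, which brackets 336. That is a separate matter and does not bear on this point.

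**Assumed inputs.** All age profiles and stool-completion rates are assumptions, shown as ranges.

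**Formula.** With control prevalence p_k at round k, completion C_k in control and I_k in intervention, and a constant true PR:

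pooled PR = PR × [Σ p_k I_k / Σ I_k] ÷ [Σ p_k C_k / Σ C_k]

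The bias is zero if p_k is flat, or if I_k is a constant multiple of C_k. Both an age trend and a gap that varies by round are needed.

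**Within the planned 15% loss.** Take 6.5 + 3.5 + 1 = 11% lost early. Let control miss 0/3/6/9% of stools, so total control loss is 1 − 0.89 × 0.955 = 15%, and let intervention miss 0/1/2/3%. With prevalence 5/15/25/35% and no effect:
- Control: 0.749/3.82 = 0.1961
- Intervention: 0.783/3.94 = 0.1987
- Ratio: 1.014

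With prevalence 12/18/22/28% the ratio is 1.007.

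**Heavier losses.** One arm completes 95/93/91/90%. The other completes 95/90/85/80% (10 points lower at 24 months) or 95/87/78/70% (20 points lower). The first value in each cell applies when intervention stools are missed late, the second when control stools are.

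| Control prevalence (%) | Late gap | True PR 1.00 | True PR 0.70 |
|---|---|---|---|
| 15/18/22/25 | 10 | 0.992, 1.008 | 0.694, 0.706 |
| 15/18/22/25 | 20 | 0.982, 1.018 | 0.688, 0.713 |
| 8/16/24/32 | 10 | 0.980, 1.020 | 0.686, 0.714 |
| 8/16/24/32 | 20 | 0.958, 1.044 | 0.671, 0.731 |
| 4/12/26/38 | 10 | 0.971, 1.029 | 0.680, 0.721 |
| 4/12/26/38 | 20 | 0.939, 1.066 | 0.657, 0.746 |

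A further steep case has prevalence 5/15/25/35%, control completing 95/88/80/70% and intervention 95/93/91/90%. Control is 0.6245/3.33 = 0.1875, intervention 0.7295/3.69 = 0.1977, ratio 1.054.

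**Type I error, by simulation.**
- The 1.054 case, 80 blocks of 10, block terms, child-clustered robust errors, 400 trials: PR 1.05 and rejection 11% without round terms; 1.00 and 6% with them.
- Profile 8/16/24/32%, 20-point gap, exchangeable GEE, 340 children per arm, no block terms, 1,000 trials: intervention stools missed late, PR 0.95 and rejection 8.1% without against 3.9% with; control stools missed late, PR 1.04 and 7.3% against 5.6%.

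**Power at PR 0.70** (second set-up, without against with round terms).
- Complete stools: 97.7% against 97.7%.
- Equal missingness: 95.8% against 96.0%. Standard errors are only about 0.5% to 1.5% smaller with round terms.
- Control stools missed late: 91.9% against 94.9% (10 points); 86.7% against 95.2% (20 points).
- Intervention stools missed late: 97.5% against 96.3% (10 points); 98.6% against 94.8% (20 points).

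The precision effect is about one point or less. The other shifts follow the direction of the bias.

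**The case against.** Much of the opposing case stands.

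- **The conditions are not documented.** A reader might infer from Participant retention that the plan expects retention to differ by arm. The text describes a countermeasure and forecasts no remaining gap, still less one that widens with age. An unblinded trial with an arm-specific payment makes differential completion plausible, no more. The Objectives say exposures change as children grow, and Study design says STH is generally more prevalent at school age, but neither gives a trend from 6 to 24 months. The listed losses are also mostly early, and a child lost before the first stool cannot change the round mix.
- **The larger scenarios exceed planned loss.** In the 1.054 case, adding 11% early loss gives 1 − 0.89 × 0.8325 = 26% in control and 1 − 0.89 × 0.9225 = 18% in intervention, about 22% overall. Counted that way, the 20% condition could be met. Counted on missed stools alone, the scenarios average about 8% to 18% per arm and it is not. Either way the weighting is exploratory and does not replace the primary estimate.
- **Lost power.** It is tempting to say that omitting round costs power. As a general statement this fails: precision barely changes, and bias can raise rejection as well as lower it.
- **Round terms as a complete cure.** They remove this bias only if missingness depends on arm and round alone and the ratio is constant over age.
- **Per-stool reading.** Table 1 and the wording of the primary indicator can also mean one ever-positive result per child, to which round terms would not apply. The exchangeable within-child matrix and the repeated-measures sample size favour one record per stool.
- **Other planned analyses.** The round-specific and interaction models would help reveal a problem, but they are secondary. A fuller analysis plan may exist; the article nonetheless states the primary model, and states it without round.

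**Conclusion.** The point holds as a modest, conditional weakness in a model the document does specify. On the per-stool reading, the pooled ratio is open to bias in either direction if prevalence changes with age and the completion gap between arms varies by round. The likely size is about 1% of the ratio within the planned 15% loss. It is 1% to 4% in mild and middle scenarios with heavier loss, and 5% to 7% when a steep trend meets a gap of about 20 points at 24 months. Rejection under no effect reaches about 7% to 11% in the larger-gap cases. All of these rest on assumed age profiles and completion rates. The document does not support saying that this bias will occur, or that the omission costs power as such. The change is worth making because it costs little and the planned safeguard is only exploratory and conditional.

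**What to change.** Include three follow-up-round indicators as main effects in the primary GEE, beside treatment and block, and still report one common prevalence ratio. Do the same in the pooled repeated-measures models for secondary outcomes. Keep treatment-by-round terms for the secondary age-specific ratios. State that the primary outcome is analysed per stool, and bring Table 1 into line. Clarify that the unadjusted primary analysis means no baseline covariates: round, like block, is a design variable.

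The cost is one pre-specified line and no new data. There are three extra parameters and a slightly higher risk that the log-binomial model fails to converge, for which modified Poisson regression is already the fallback. With complete or equally missing stools the ratio is essentially unchanged. The change should be fixed before unblinding, since adding it after seeing unequal completion would look data-driven. It does not correct missingness that depends on infection, and corrects only partly if the ratio varies with age, so the attrition comparison and censoring-weight analysis remain useful.

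### The weighted analysis for dropout bias runs only if attrition differs by arm and also exceeds an undefined 20%, above the 15% loss the protocol plans for

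*Protocol article*

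**What the plan says.** All of the following is in the protocol article.

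- **Statistical analysis, unconditional step.** "We will compare attrition rates at each follow-up and across follow-ups between randomised arms". The same sentence also promises a baseline comparison of those lost with those who complete.
- **Statistical analysis, conditional step.** "If there is evidence of systematic differences in attrition between arms and attrition exceeds 20" per cent, then "we will explore whether study drop out resulted in selection bias using inverse probability of censoring weights". The two conditions are joined by 'and'. No denominator is given for the 20%. In the same section, by contrast, the trigger for the per-protocol analysis is stated as 10% non-compliance in one arm or the other.
- **Sample size calculation.** "15% loss to follow-up was assumed based on the findings from the prior trial carried out by our team in rural Bangladesh". The components cited are: "6.5% of pregnant women miscarried or had still births, 3.5% of children died by 12-month follow-up, and <1% died between 12-24 months follow-up".
- **Participant retention.** "To minimize attrition in the control arm, we will compensate mothers from control households with 500 Bangladeshi Taka", paid after each follow-up survey. No matching payment to intervention mothers is described.
- **Other analyses.** The primary analysis is unadjusted. All models condition on geographic block. A secondary analysis adjusts for baseline covariates associated with the outcome.

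**The concern.** The plan names a method for examining dropout bias and then sets the bar for using it above its own expected loss. On one natural reading of the 20%, the team could see clear differential attrition in its own tables and, under the written rule, still not run the analysis.

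The first condition is also a weak screen. Selection bias depends on who is lost in each arm, and equal percentages can hide different kinds of children. The protocol gives reasons to take that seriously: participants are unblinded, only control mothers are paid per visit, and only intervention households move out for about two weeks during installation. The unconditional baseline comparison sets those lost against completers. As worded it is not split by arm, so it need not reveal such a pattern.

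At stake is whether readers of the primary prevalence ratio get a weighted companion estimate when loss is below 20%.

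**Working it through.** **1. The plan's own attrition figure.** The sample size section states that "the required number of households per arm is 336". Inflating for 15% loss gives 336 / 0.85 = 395.3, so 396 per arm. Rounding up to whole blocks of 10 (5 per arm) gives 400 per arm and 800 in total, as stated. The components cited for the 15% sum to at most 6.5 + 3.5 + 1 = 11 points.

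**2. How often the rule fires.** Inputs: 400 per arm, binomial losses. My assumption: 'evidence of systematic differences' means a two-sided 5% test of two proportions. Probabilities are summed exactly over the two binomial counts.

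For the 20% condition alone, read as overall attrition, at least 161 of 800 must be lost:

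| True loss, both arms | P(overall loss > 20%) |
|---|---|
| 15% | 0.00006 |
| 18% | 0.066 |
| 20% | 0.48 |

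For both conditions together:

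| Loss by arm (mean 15%) | P(arms differ) | Rule fires, 20% = overall | Rule fires, 20% = either arm |
|---|---|---|---|
| 15% v 15% | 5% | 0.0003% | 0.3% |
| 12% v 18% | 66% | 0.004% | 13% |
| 10% v 20% | 98% | 0.005% | 47% |
| 5% v 25% | about 100% | 0.003% | 99% |

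On the overall reading, imbalance makes almost no difference, because the total stays near 15%. On the either-arm reading, only strong imbalance makes the rule likely to fire.

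**3. Illustrative size of the bias.** None of the risk assumptions here comes from the protocol. Take no true effect and a true prevalence of p = 20% (the protocol's control assumption) in both arms. Let a be the fraction lost, and r the prevalence in lost children relative to retained children. Then

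observed prevalence = p / ((1 − a) + a·r)

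and the observed prevalence ratio (PR) is intervention over control.

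- Loss 20% intervention and 10% control, r = 2 in both: (0.2/1.2) / (0.2/1.1) = 0.92.
- Same loss, control loss at random: (0.2/1.2) / 0.2 = 0.83. With r = 1.5 in the intervention arm: (0.2/1.1) / 0.2 = 0.91.
- Loss 15% in each arm, r = 2 in the intervention arm only: (0.2/1.15) / 0.2 = 0.87.

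The design PR is 0.70. On the log scale, ln 0.83 / ln 0.70 is about 0.51, so the most extreme of these cases covers about half the distance from no effect to the design effect.

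**4. The same formula if most loss is pregnancy loss or death.** If 11 of the 15 points never become surviving children with a missing stool, about 4 points remain (an assumption; missed stools would add to it).

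- Equal 4% loss, r = 2 in the intervention arm only: 1/1.04 = 0.96.
- 5.3% v 2.7% loss, r = 2 in both: 1.027/1.053 = 0.98.

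**The case against.** A reader might infer three stronger things that the protocol does not support.

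- **That dropout goes unexamined.** It does not. Attrition rates by arm, and the baseline characteristics of those lost, are compared without condition. Only the weighting step is gated.
- **That the models have no other protection when missingness depends on baseline characteristics.** They have some. Every model conditions on block, and an ungated secondary analysis adjusts for baseline covariates that predict the outcome. If missingness runs through those covariates and the model is right, that analysis addresses it. The protection is partial: its stated aim is chance imbalance (and efficiency), covariates are chosen by association with the outcome and not with dropout, and the primary analysis is unadjusted.
- **That the rule can never fire at 15% loss.** That is true in practice only if 20% is overall. On an either-arm reading, strong imbalance could trigger it.

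The case against the magnitude also has force. The PRs of 0.83 to 0.92 treat all loss as surviving, higher-risk children, whereas the sample size section accounts for about 11 of the 15 points by pregnancy loss and death. They also show total selection bias. Weights built on baseline covariates would remove only the part those covariates explain. That the payment changes who stays in the control arm is plausible but not documented.

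Finally, a contingency set above expected loss is not in itself an error, and how censoring is coded can be left to an analysis plan. That stands for the coding. It does not excuse a published rule that requires both conditions and leaves its threshold undefined.

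**Conclusion.** The point holds as a badly set decision rule. The IPCW analysis needs differential attrition and attrition above 20% together, with planned loss at 15% and no denominator given. On the overall reading it would almost never run at the planned loss, even at 10% v 20% (about 0.005% of trials). On the either-arm reading it would run in about 47% of such trials and 13% at 12% v 18%. Neither reading covers similar loss rates with different children lost. These probabilities rest on binomial losses and a 5% test as the evidence of a difference.

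The consequence is a withheld sensitivity analysis. Nothing in the protocol shows the primary estimate to be wrong. The bias figures are illustrations at the upper end and shrink to about 0.96 to 0.98 if only some 4 points of the loss are surviving children. This is a cheap improvement worth making, not a flaw that threatens the design.

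**What to change.** Delete both conditions. Report the IPCW estimate as a pre-specified sensitivity analysis beside the unweighted primary result in all cases, with weights from baseline covariates and block. Count missing stool at each of the four rounds among live-born children as censoring, and state how rounds after a child's death are handled. If attrition thresholds are kept for any descriptive purpose, say what they refer to: overall, per arm, per round or cumulative.

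The method is already named in the protocol, so the cost is about one sentence and a little more analysis work. The downside is one more estimate to report, with somewhat wider intervals from the weights. Sample size and primary analysis do not change.
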